# Assessing the Feasibility of a Multicenter Transition Intervention Model Across Adolescent Secure Services in England (MOVING FORWARD): Protocol for a Feasibility Cluster Randomized Controlled Trial

**DOI:** 10.2196/29273

**Published:** 2021-10-22

**Keywords:** transition, intervention, young people, feasibility cluster randomized trial, cluster randomized controlled trial, secure hospitals, outcomes, adolescents, patients

## Abstract

**Background:**

Young people moving from adolescent secure inpatient units to adult care in the United Kingdom have multiple and complex needs and are more likely to experience poor transition outcomes. Poorly managed transitions can lead to enduring use and dependency on mental health services. However, there is a lack of knowledge about the feasibility of transitional care models.

**Objective:**

This paper presents the protocol for a study that aims to test a feasibility cluster randomized controlled trial for young people transitioning from adolescent secure services to adult-oriented settings. The overarching aim of the MOVING FORWARD study is to provide a preliminary estimate of the effectiveness and cost-effectiveness of a new transition intervention model and to inform a future full-scale cluster randomized controlled trial.

**Methods:**

The design of the study is a 3-arm feasibility cluster randomized controlled trial comparing the MOVING FORWARD intervention against standard transition preparation conducted at 6 adolescent secure services, of which 4 units will receive the intervention and 2 will serve as controls. Eligible young people between 17-19 years, their parents/carers, and key workers will be invited to participate. Young people and parents/carers will be allocated to two conditions (young people alone and young people with a parent/carer) and will receive 4 transition preparation workshops across 6 months. Six adolescent secure hospitals will be randomly allocated, stratified by area and service type. Data will be collected at 3 time points: baseline (T0), 6-12 months postintervention (T1), and 18-24 months postbaseline (T2). Primary and secondary outcomes will be based on assessment measures and interviews conducted at T1 and T2.

**Results:**

A total of 13 young people and 17 staff members have contributed to the intervention design through online advisory groups on the design of the study and important themes for transition. We have also consulted members of the public (a steering group) including 2 young people who have transitioned to the community and 2 parents/carers. Common identified themes included appropriateness of module content and support during delayed transitions. The content of the intervention will be finalized during the first 6 months of the study. Participants will be recruited over the course of 6 months. An intraclass correlation coefficient will be calculated to inform the power of the sample size for a further large-scale trial. With a sample size of 50, we will be able to estimate a dropout rate of 80% (95% CI –11% to 11%).

**Conclusions:**

This research will provide practitioners and policy makers with an evidence-based framework of how training and familiarization with the prospective transitions can yield positive outcomes. This study will test whether a psychosocial intervention can be implemented in adolescent secure hospitals. The results will identify barriers and facilitators to the proposed intervention and will enable services to reflect on the quality of transitional care delivery.

**International Registered Report Identifier (IRRID):**

PRR1-10.2196/29273

## Introduction

### Background

Previous research has classified transitions as a global priority for chronic conditions [1]. There is substantial evidence that transitions from pediatric services to adult care in the United Kingdom are linked to the exacerbation of medical and mental health symptoms and poor life opportunities [2]. Young people moving from inpatient (tier 4) child and adolescent mental health services to adult-centered settings are more likely to experience poorly planned transitions due to inconsistent care and low transition readiness [3]. Fundamental differences in treatment approaches and care priorities have created a substantial gap between child and adult services and, coupled with low transitional readiness, have been found to be major barriers to positive transition outcomes [4]. Transitional care is particularly poor for young people in adolescent secure services, most of whom are detained under the jurisdiction of the Mental Health Act due to offending, and present with multiple comorbidities (including emerging personality disorders, neurodevelopmental and learning disabilities, and psychosis), for which many already experience prolonged stays in hospital [5]. As of 2016, there were 1283 young people in secure hospitals across England; approximately 43% of this cohort did not have a placement address when transitioning to the community [5]. Adolescents in these services, including medium and low secure units and psychiatric intensive care units (PICUs), constitute a neglected research and clinical group despite their multitude of needs and disadvantage (social adversity, trauma, high risk, and vulnerability).

Young people in contact with the youth justice system are more likely to experience multiple transitions across a range of services, including secure establishments to secure inpatient hospitals [6]. Six percent of young people in secure care have been in 10 or more placements before moving to inpatient secure hospitals [5]. Each setting follows different principles in their care approach and delivers different treatment models to the young people they accommodate. These constant changes in principles and care are particularly harmful and challenging for young people with learning disabilities, autism [6], and other neurodevelopmental disorders.

### The Need for a New Transition Model

There remains a dearth of research aiming to develop, implement, and evaluate transitional care models [6]. Effective and supportive transitions foster independence in young people and facilitate confidence in their treatment. The National Institute for Health and Care Excellence (NICE) 2016 guidelines explicitly state that self-efficacy (managing one’s own health) is a key priority for service commissioners and policy makers, and recommend evidence-based research in the form of cluster randomized controlled trials (cRCTs) in self-management training to improve transition preparation for special groups [7]. This study aims to address this gap and improve current processes for young people transitioning from adolescent secure services to adult-oriented care by (1) developing a psychosocial transition intervention with a developmental focus and (2) assessing the feasibility of undertaking a future trial of its clinical and cost-effectiveness.

Fragmented support during transitions can lead to enduring use and dependency on mental health services pertinent to long-term financial burden, limited employment opportunities and social functioning [8], as well as high reoffending rates and reinstitutionalization [5]. As such, transitional care has become a national priority in the United Kingdom to minimize the risk of poor transition preparation and increase positive outcomes. Recently developed practice guidelines on care transitions from adolescent secure services to adult services stress the importance of graded and flexible transitions aiming for a needs-based care model, contrasting to the age-based approach currently in use [9]. However, most available interventions are in line with adult models of care and may fail to include developmental perspectives [5], and there are no interventions or guidance targeting transitional care in secure settings. In addition, there remains a lack of well-defined planning and knowledge about the feasibility of specific models of transitional care that can reduce the public health burden of emerging adults at risk. The implementation of systematic interventions during institutional and health care transitions is highly likely to be cost-effective considering the costs associated to enduring mental health issues and secure hospital admission. This research is timely and falls within the scope of the National Health Service (NHS) Five Year Forward View in implementing new models of care for young people within the capacity of “personalized care” and borne from coproduction, whereby individuals are empowered using a strength-based approach. The research also aligns with the NICE 2016 guidelines, the Care Act 2014, the National Institute for Health Research (NIHR) infrastructure, and the NIHR Applied Research Collaboration South London, aiming to improve health care services for young people.

### Evidence for the Proposed Intervention

The proposed developing intervention is based on previous effectively established and implemented intervention models, including cognitive behavior therapy (CBT), parent-child interaction therapy, attachment-based therapy, social skills training (SST), and psychoeducational elements, which target self-efficacy and management of mental health and conduct problems tailored around goal-oriented approaches. SST and CBT group-based interventions are particularly effective in young people with autism [10]. Elements from these well-established approaches will contribute to behavior change in young people in secure care via upskilling them and building a goal-oriented approach toward their discharge. For example, elements from attachment-based and trauma-informed models will be used to increase confidence among young people and facilitate the “letting go” process. There is compelling evidence that these therapeutic models are effective for young people with challenging behaviors and complex trauma histories like those in secure care [11-14]. The current intervention will contribute to self-efficacy upon discharge. Key transition workers will be trained to deliver this intervention considering they are key attachment figures for young people. The intervention will start 6 months before they turn 18 years of age to allow time to prepare and avoid abrupt transitions. These interventions are more likely to be brief and successfully delivered in clinical settings, as in the proposed feasibility trial [13]. Group-based interventions delivered to young people with neurodevelopmental needs and mental health problems have shown increased self-determination and social functioning [15-18].

### Aims and Objectives

The MOVING FORWARD study aims to implement a new transition intervention model for young people transitioning from adolescent secure services to adult-oriented settings and test the feasibility of a future cluster trial measuring its effectiveness. The primary objectives are (1) to finalize the development of the intervention; (2) to determine the feasibility of conducting a full cRCT in adolescent secure inpatient units; (3) to test the feasibility and acceptability of trial procedures and materials, including recruitment, randomization, allocation, assessment tools, response rates, adherence and follow-up across 6 sites; (4) to determine the appropriateness of the proposed outcome measures; (5) to describe treatment as usual (controlled condition) across all sites; and (6) to qualitatively explore the views and experiences of health care staff delivering the intervention.

## Methods

### Intervention Development

Figure 1 illustrates the coproduction plan and refinement process of the MOVING FORWARD intervention [19]. The intervention is in the process of development and will be finalized in the first 6 months of the study with the help of the steering and stakeholder groups, which were set up in the first and second stages of the coproduction phases. As of July 2021, the advisory groups have agreed on the overarching themes leading the 4 workshops: transition literacy; future plans; goal management; and expectations, attachment, and self-efficacy (Table 1). This research builds on an early career researcher grant awarded by Kingston University, which established advisory groups to coproduce a transition intervention for young people transitioning from adolescent secure services to adult services and their families. Advisory groups were set up with 13 young people with a previous, current, or upcoming transition experience from adolescent secure services to adult services, 2 parents of young people who had experienced this transition, and 17 staff from adolescent secure services. This study aims to implement this modular intervention and test the feasibility of a full clinical trial.

**Figure 1 figure1:**
[figure not shown]
Development and refinement of the MOVING FORWARD intervention.

**Table 1 table1:** Intervention themes and workshop content.

Intervention	Theme	Aims	Module tasks
Workshop 1	Transition literacy	Participants will be asked whether they understand the purpose of moving to adult services or an adult-oriented community and how they envision a positive transition. The elicited themes will inform the subsequent stages of the intervention	Role playing, vignettes/scenarios, videos, reflective discussion and writing, skills management
Workshop 2	Future plans	Participants will focus on education, employment, overall well-being, housing, and community living	Role playing, vignettes/scenarios, videos, reflective discussion and writing, skills management
Workshop 3	Goal management	Participants will be introduced to mental health symptom and risk management when in crisis, relapse and reintegration, support services, peer support, and role models and mentors	Role playing, vignettes/scenarios, videos, reflective discussion and writing, skills management
Workshop 4	Expectations, attachment, and self-efficacy	Participants will focus on what to expect in adult services, what difficulties they might encounter, what being an adult encompasses, what new responsibilities they will face depending on the type of placement they are admitted to, how the therapeutic style and alliance might change, parental involvement, hospital/community routine and structure, and older peers	Role playing, vignettes/scenarios, videos, reflective discussion and writing, skills management

### Feasibility Trial Design

This study is a mixed methods, multicenter, 3-arm, feasibility cRCT with a parallel design comparing the MOVING FORWARD intervention against standard transition preparation (usual care: Care Programme Approach [CPA] discharge and individual meetings with the responsible clinician) conducted at 6 adolescent secure sites, of which 4 units will receive the intervention and 2 will serve as controls. Young people across these adolescent secure services present with similar mental health and neurodevelopmental needs and complex trauma history. In this specific study, we will focus on those with emerging borderline personality disorder, psychosis, autism, learning disabilities, and conduct disorder. Data will be collected at 3 time points: baseline (time 0; T0), 6-12 months postintervention (time 1; T1), and 18-24 months postbaseline (time 2; T2). A cRCT will minimize the risk of contamination, which is high in the proposed study as elements from the intervention could be used for standard transition preparation.

A feasibility study will measure the acceptability of conducting a future, fully powered trial across different pools of young people in secure care and different settings across adolescent secure hospitals. This study will test how the future trial will look like, as well as the main research question and primary outcomes. Outcome measures and one-to-one semistructured interviews with young people, parents/carers, and health care staff will be conducted to explore the experiences of young people receiving the intervention and those who received treatment as usual (TAU). The practicality and integration of the intervention within the current system of care and use of resources will be explored with the participants. A total of 30 interviews will be sought to understand the mechanisms of impact.

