### Trial Conditions

#### Condition 1: T0 Baseline Pretransition (6-12 Months Before 18th Birthday)

As discussed with the advisory groups in the first stage of the coproduction/development phase, this intervention will include 4 modules delivered over 8 series of 2-day workshops. When the intervention is finalized, a manual will be developed including the goals and objectives of each workshop, skills developed, behavior expectations and management, themes that need to be covered, required materials for the sessions, and strategies for young people with neurodevelopmental needs. The content of the sessions will be the same across different groups of patients although adjustments will be applied to the intervention models based on each group’s mental health and developmental needs identified during the piloting phase with the lead sites (Ardenleigh and St Andrews). These adjustments will be discussed with the steering group to ensure that the intervention fidelity is not threatened. Additionally, monitoring procedures with the help of the research team across the study will enhance intervention fidelity. For example, young people with neurodevelopmental needs may need additional help in terms of mental health literacy and understanding the purpose of their prospective transition. The workshops will be delivered across 4 days, and there will be 4 sessions targeting different domains of transition. Staff members who attended the transition training will deliver these workshops as they are key attachment figures to the young people. Each workshop will take between 30-40 minutes. Key workers from the advisory groups suggested that the intervention should be informed by attachment-based therapy, CBT, SST, and psychoeducational elements, which target self-efficacy and management of mental health problems.

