#### Conditions 1-3: T1 (6-12 Months Posttransition)

Young people and parents/carers (condition 2) who received an intervention and those who received care as usual (condition 3) will be visited and interviewed at the receiving placement 6-12 months postdischarge. Outcome measures will be completed.

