#### Conditions 1-3: T2 (18-24 Months: Endpoint)

Young people and parents/carers (condition 2) who received the interventions and those who received care (condition 3) as usual will be followed up depending on an old or new placement and will be interviewed about continuity of care, mental health, overall well-being, education, employment, and relapse. Outcome measures will be completed.

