### Participants

#### Young People

A total of 50 participants will be recruited on a rolling basis over 6 months from the commencement of the study. Any young person meeting the inclusion criteria listed below irrespective of their gender, ethnicity, religion, education, and disability status will be eligible for inclusion:

If aged ≥17 years and eligible for transition from an adolescent secure hospital, including those experiencing delayed transitions;If formally diagnosed with a mental disorder, and/or learning disability, and/or neurodevelopmental problem.

Any young person meeting the following criteria will be not eligible for inclusion:

If presenting with moderate intellectual impairment with an IQ<65;If in an acute phase of severe mental illness;Cannot provide consent due to physical disabilities and/or language problems or any other neurodevelopmental deficits.

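### T1 is dated from the intervention in one place and from discharge in another, and T2 from baseline, so no T1 date exists for every participant and T1 can precede, overlap or follow T2

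*Protocol article*

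**What the plan says.** The Abstract (Methods) and the Feasibility Trial Design section agree with each other. The Abstract lists "baseline (T0), 6-12 months postintervention (T1), and 18-24 months postbaseline (T2" and the design section repeats it as "6-12 months postintervention (time 1; T1), and 18-24 months postbaseline (time 2; T2". T1 therefore counts from the intervention and T2 from baseline.

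The T1 subsection of Trial Conditions uses another clock. Its heading is "Conditions 1-3: T1 (6-12 Months Posttransition", and its text says that participants "will be visited and interviewed at the receiving placement 6-12 months postdischarge". It explicitly includes TAU: "those who received care as usual (condition 3) will be visited and interviewed at the receiving placement". The matching T2 subsection is headed "Conditions 1-3: T2 (18-24 Months: Endpoint" and gives no starting point.

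Three other statements bear on the timing:
- The Condition 1 heading places baseline as "T0 Baseline Pretransition (6-12 Months Before 18th Birthday". The headings for Conditions 2 and 3 carry no birthday wording.
- The eligibility list under Young People takes participants aged 17 or more who are due to move, "including those experiencing delayed transitions". It sets no limit on the delay. The Abstract gives the age range as 17 to 19.
- Progression Criteria and Feasibility Outcomes asks for follow-up of at least 70% at T1 and 60% at T2, and applies the same thresholds to acceptability of the assessment tools.

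**The concern.** The two T1 definitions count from different events, and neither event happens to everyone enrolled. TAU has no intervention to count from. A young person whose move is delayed may have no discharge to count from. Discharge also occurs after randomization and could be affected by transition preparation, so a T1 tied to discharge can select different participants, at different times since baseline, in different arms.

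Because T2 counts from baseline, nothing in the text keeps the two visits apart. Two things depend on that. First, the follow-up and tool-acceptability criteria need a rule for who is due, on time or missed at each visit. Second, TROM, on which the Quantitative Analysis section bases the sample size of the definitive trial, is collected only at T1 and T2. Its variance and intraclass correlation would mix unlike follow-up times.

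**Working it through.** The plan states no derived figure for visit timing, so the check puts each T1 wording on T2's clock. All times are months after baseline, and T2 = 18 to 24.

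Inputs from the protocol:
- T0 is 6 to 12 months before the 18th birthday (Condition 1 heading).
- The intervention starts 6 months before the 18th birthday (Evidence for the Proposed Intervention), so on that wording it starts s = 0 to 6 months after T0.
- Course length L is 6 months in the Abstract and 4 days (about 0 months) under Condition 1. These two statements conflict.
- No discharge date is given. Discharge at the 18th birthday is an assumption; it puts discharge at D = 6 to 12.

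Post-intervention clock: T1 = s + L + 6 to s + L + 12.

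Post-discharge clock: T1 = D + 6 to D + 12.

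| Reading | Arithmetic | T1 | Against T2 (18-24) |
|---|---|---|---|
| 4-day course at T0 | 0+0+6 to 0+0+12 | 6-12 | wholly before |
| 6-month course from T0 | 0+6+6 to 0+6+12 | 12-18 | touches at month 18 |
| 6-month course, s = 0 to 6 | 0+6+6 to 6+6+12 | 12-24 | covers all of T2 |
| Discharge at 18, D = 6 to 12 | 6+6 to 12+12 | 12-24 | covers all of T2 |
| Discharge 6 months after 18, D = 12 to 18 | 12+6 to 18+12 | 18-30 | covers T2 and runs past it |
| Discharge 18 months after 18, D = 24 to 30 | 24+6 to 30+12 | 30-42 | wholly after |

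Rows with a range for s or D span participants with different baseline timing. One person's T1 window is 6 months wide.

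General rule on the discharge clock:
- T1 closes before T2 opens if D + 12 < 18, that is D < 6. At D = 6 the windows touch.
- T1 lies wholly after T2 if D + 6 > 24, that is D > 18.
- For D above 6 and up to 18 the windows meet or overlap. At D = 12 they are identical (18-24).

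Who has a T1 date:

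| Participant | Post-intervention wording | Post-discharge wording |
|---|---|---|
| Intervention, discharged | yes | yes |
| Intervention, not discharged | yes | no |
| TAU, discharged | no | yes |
| TAU, not discharged | no | no |

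Progression criteria with the target of 50 young people: 0.70 × 50 = 35 at T1 and 0.60 × 50 = 30 at T2. One participant is 1/50 = 2 percentage points. Each person left out as not yet due for T1 lowers the number required by 0.7.

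Baseline: 6 to 12 months before the 18th birthday means age 17 to 17½. A participant already 18 or over cannot meet that definition.

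**The case against.** The best defence is that the article gives enough for a workable schedule. The T1 subsection names all three conditions and supplies a discharge date for TAU. Under the other wording, treated participants still in hospital do have a T1. A short course at baseline, or discharge within 6 months of baseline, puts T1 before T2. A study team would in practice schedule one person's visits in order. The natural denominator for the follow-up criteria is everyone recruited. The trial diagram, which is not shown here, may state the schedule.

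Much of this stands, and it limits what can be claimed. A reader might infer any of the following, and none is supported:
- That the control arm simply lacks a T1. That is so only under the Abstract and Feasibility Trial Design wording.
- That nobody undischarged has a T1. That follows for all arms only under the discharge wording.
- That T1 must overlap or follow T2, or that any delayed transition puts T1 after T2. The table shows readings with no overlap, and T1 is wholly after T2 only when D exceeds 18.
- That a stated percentage of T1 visits would fall after T2. This would need discharge dates, which the protocol does not give, and an assumption that one person's visits are dated independently.
- That baseline is unworkable throughout. The birthday wording is only in the Condition 1 heading.

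The defence does not remove the conflict. Two printed T1 definitions disagree, each fails for an identifiable group, and the undischarged TAU participant is missed by both. The diagram could add a schedule, but the contradictory text would still need correcting.

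**Conclusion.** The point holds as an inconsistency in visit definitions. T1 has two anchors, T2 has a third in two places and none in its own subsection, and no T1 anchor exists for every eligible participant. T1 can fall anywhere from months 6-12 to wholly after T2, depending on the wording followed and the discharge date. The 12-24 range on the discharge clock assumes discharge at age 18. The thresholds D < 6 and D > 18 need no such assumption.

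The consequences are a between-arm comparison that may be made at different times, a T1 that on one reading depends on a post-randomization event, and follow-up criteria whose visit windows are not fixed. It should be settled before recruitment, because a visit missed under an unclear window cannot be recovered later. The Condition 1 baseline wording is a smaller, related defect.

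**What to change.** Reconcile the Abstract, Feasibility Trial Design, the Condition 1 heading and the T1 and T2 subsections of Trial Conditions to one anchor that exists in all three arms. The simplest is the baseline date, defined as the date of consent, which also works for participants already 18 or over. The two statements of course length must also be reconciled, although with a baseline anchor the visit dates no longer depend on them.

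- Set windows so that T1 closes before T2 opens. The exact T1 window is the sponsor's choice; 12 months is one example.
- Hold both visits whether or not discharge has occurred, and record the discharge date.
- Count follow-up for the 70% and 60% criteria against all recruited participants.
- Report the proportion transitioned by arm. Treat TROM and the psychosocial adjustment scale (PARS-III) among those transitioned as descriptive, because that subset is selected after randomization.

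This goes beyond rewording. Time since discharge at T1 will vary, and some participants will be assessed before they move. With discharge assumed at D = 6 to 12, a 12-month T1 falls 12 − 12 = 0 to 12 − 6 = 6 months after discharge, not 6 to 12. If discharge is 6 months later (D = 12 to 18), almost nobody has moved by then. Fewer participants will therefore have TROM at T1, and the sponsor should allow for this when planning the variance and intraclass correlation estimates.
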